**6.2 Preparation/Handling/Storage/Accountability**

**6.2.1 Acquisition and Accountability**

CSL Behring will ship an initial drug supply based upon an estimated patient weight (eg. 80 kg) for the first 2 study subjects using 20ml and 10 ml vial sizes. CSL Behring will work with the study site to determine the best vial sizes per study subject needs. For all remaining study subjects, the study site will be in close contact with CSL Behring to provide specific drug supply as needed.

NEED TO ASK [name] regarding how we will receive Hizentra (how much at what time). Hizentra will be stored in a locked clinical research facility and will be dispensed to subjects once monthly once they are comfortable self-administering at home. Hizentra will be stored at room temperature for the entirety of its shelf life, up to 30 months.

**6.2.2 Formulation, Appearance, Packaging, and Labeling**

Hizentra will be dispensed to subjects once monthly and will be stored at room temperature.

**6.2.3 Product Storage and Stability**

Hizentra will be stored at room temperature for the entirety of the study.

**6.2.4 Preparation**

Hizentra will be infused from each vial with the assistance of an infusion pump per 6.1.2.

**6.3 Measures to Minimize Bias: Randomization and Blinding**

Given the study design: single center case series, there will be no randomization or blinding for the study.

**6.4 Study Intervention Compliance**

Adherence to the protocol will be monitored by regular communication between subjects and the investigators and clinical research coordinators. Reminder phone calls will be made to patients for timely lab testing, and patients will complete an SF 36 at defined study visits.

**6.5 Concomitant Therapy**

Subjects will be allowed to continue all concurrent medical therapies during the entirety of the study. As per the exclusion criteria, Ig replacement from outside the study is not allowed at any time. Subjects will also be asked to report the use of any antibiotic courses during the study.

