**2.2 Background**

Lymphoproliferative disorders (LPD) are one of the most common hematologic malignancies. Each year in the U.S., approximately 15,000 patients are diagnosed with chronic lymphocytic leukemia (CLL). [1] Patients with CLL are at increased risk of infections as compared to age matched controls. [2] Furthermore, infections remain a major cause of morbidity and mortality, with up to 17% to 50% of infections being fatal. [2-4] Infection type and occurrence in CLL are related to disease stage and treatment history. CLL carries a known increased risk of bacterial infections, but certain anti-neoplastic agents increase the risk of viral infections, while the Bruton kinase inhibitor ibrutinib may decrease rates of infection. [5] Attempts at decreasing infections in CLL have included therapy with prophylactic antibiotics and intravenous immunoglobulin. In general clinical practice and in previous studies, patients have started immunoglobulin replacement therapy if they have a history of serious infection or hypogammaglobinemia (defined as IgG below 400 g/dL). [4-8] Immunoglobulin replacement therapy has been shown to decrease rates of bacterial infection in some studies, but the utility of the universal application of the practice remains unclear. A Cochrane meta-analysis concluded that the use of IVIG may be considered in patients with LPD with hypogammaglobinemia and recurrent infection, but acknowledged that the studies are heterogeneous. [9]

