**4.4 End of Study Definition**

A subject is considered to have completed the study if:

- They have a normal immune evaluation
- They have an abnormal immune evaluation and complete 6 months of therapy with subcutaneous Ig followed by the laboratory evaluation following a 3 month wash out period.

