**5.2 Exclusion Criteria**

Any subject who meets any of the following criteria will be excluded from the study:

- Previously diagnosed primary immunodeficiency
- Additional immunosuppressive states as assessed by the primary or co-investigators
- Ongoing therapy with Ig replacement
- Serum IgG < 400 mg/dL

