**6.1.2 Dosing and Administration**

Each subject will be treated with a fixed dose of subcutaneous Hizentra 100 mg/kg/week for 24 weeks. Hizentra will be administered at the study site until patients are comfortable with self-administration at home. Typically, this will take 2-3 sessions on site with the assistance of the clinical research coordinator. Once patients are self-administering at home, they can administer at any time of day. There will be no defined relationship to administration of Hizentra in regards to meals. All subjects will discontinue Hizentra after 24 weeks of therapy, and will subsequently monitored for a 3 month wash out period. The specific dose of Hizentra may be adjusted due to significant changes in weight during the study time period.

Subjects will be advised regarding the following points regarding administration:

- Prior to administration, visually inspect each vial of Hizentra for particulate matter or discoloration, whenever the solution and container permit.
- Do not freeze. Do not use any solution that has been frozen.
- Check the product expiration date on the vial label. Do not use beyond the expiration date.
- Do not mix Hizentra with other products.
- Do not shake the vial.
- Use aseptic technique when preparing and administering this product.
- The Hizentra vial is for single-use only. Discard all used administration supplies and any unused product immediately after each infusion in accordance with local requirements.

Subjects will be advised regarding the following points regarding dosing:

- Hizentra is intended for subcutaneous administration using an infusion pump.
- Infuse Hizentra in the abdomen, thigh, upper arm, and/or lateral hip.
- Infusion sites – A Hizentra dose may be infused into multiple infusion sites. Use up to 8 infusion sites in parallel. More than one infusion device can be used simultaneously. Infusion sites should be at least 2 inches apart. Change the actual site of infusion with each administration.
- Volume (as tolerated) *–* For the first infusion of Hizentra, do not exceed a volume of 15 mL per infusion site. For subsequent infusions, the volume may be increased to 25 mL per infusion site.
- Rate (as tolerated) *–* For the first infusion of Hizentra, the recommended flow rate is up to 15 mL per hour per infusion site. For subsequent infusions, the flow rate may be increased to 25 mL per hour.

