**6.5.1 Rescue Medication**

The study site will not be providing any rescue medications for the purposes of this study.

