**7.2 Participant Discontinuation/Withdrawal from the Study**

The study intervention will be discontinued at any time a patient wishes to withdraw for any reason. Subjects will continue with medical care as prior to study enrollment.

All efforts will be made to continue to follow patients even if they are no longer receiving study drug. Study subjects may be withdrawn at any time based on the discretion of the investigator for safety, behavioral, or administrative reasons (including, but not limited to, an adverse event, lymphoma progression, protocol deviation, loss to follow up, non-adherence, or study termination).

In accordance with International Conference on Harmonisation (ICH) principles of Good Clinical Practice (GCP) the investigator always has the option to advise a subject to withdraw from the study over concerns of safety or subject well-being.

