**10.1.8 Protocol Deviations**

A protocol deviation is any noncompliance with the clinical trial protocol, International Conference on Harmonisation Good Clinical Practice (ICH GCP), or Manual of Procedures (MOP) requirements. The noncompliance may be either on the part of the participant, the investigator, or the study site staff. As a result of deviations, corrective actions will be developed by the site and implemented promptly. These practices are consistent with ICH GCP. The site investigator will identify and report deviations within 2 working days of identification of the protocol deviation, or within working days of the scheduled protocol-required activity. Protocol deviations will be sent to the reviewing Institutional Review Board (IRB) per their policies.

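### The ban on outside Ig runs through washout with no clinical-need exception, and with only a per-protocol dataset a patient could drop out of the summaries because of the infection being counted

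*Protocol*

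**What the plan says.** Section 6.5 of the protocol, on concomitant therapy, reads: "As per the exclusion criteria, Ig replacement from outside the study is not allowed at any time". The only criterion in 5.2 about receiving Ig is "Ongoing therapy with Ig replacement".

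Section 6.1.2 ends study treatment for everyone: "All subjects will discontinue Hizentra after 24 weeks of therapy". A 3-month washout follows. Section 6.5.1 adds: "The study site will not be providing any rescue medications for the purposes of this study".

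On ordinary practice, 2.2 reports that "patients have started immunoglobulin replacement therapy if they have a history of serious infection or hypogammaglobinemia (defined as IgG below 400 g/dL"). The same section says that the value of universal use is unclear. Section 8.2 leaves serious adverse events to the investigators or the patient's other doctors, treated as they usually would be.

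On consequences, 10.1.8 says: "A protocol deviation is any noncompliance with the clinical trial protocol". Section 7.2 allows the investigator to withdraw a patient for reasons that include "an adverse event, lymphoma progression, protocol deviation, loss to follow up, non-adherence, or study termination". Under 4.4, a patient with an abnormal evaluation completes the study only if they "complete 6 months of therapy with subcutaneous Ig followed by the laboratory evaluation following a 3 month wash out period".

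Section 9.3 names a single analysis set, a per-protocol one, and does not define it. Section 9.4.4 makes the safety analysis descriptive and names no other population.

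**The concern.** The treated patients are selected for impaired antibody responses, are given Ig for 24 weeks and are then taken off it. A serious infection in washout is foreseeable in this group. By the protocol's own account of practice, it is a recognised reason to start Ig. Any Ig given then is outside Ig, and 6.5 forbids it without exception.

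Two things are at stake. The first is care: 6.5 and 8.2 give the treating doctor different instructions for the same patient. The second is the analysis. The secondary objectives include tracking infections that need antibiotics, safety and tolerability, and SF-36. If a serious infection leads to Ig, the Ig is a deviation, and the deviation removes the patient from the only named dataset, then the exclusion was caused by the outcome. The infection and adverse event summaries would then be biased downward.

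**Working it through.** **Step 1. Does the cited criterion support the ban?** Section 5.2 lists ongoing Ig replacement as a reason not to enter the study. It does not address Ig started after entry. The extension to the whole study comes from 6.5 alone.

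**Step 2. Is there a compliant route in washout?**
- Study Ig: stopped for all at 24 weeks (6.1.2).
- Rescue from the site: none (6.5.1).
- Outside Ig: barred (6.5).
- Section 7.1: covers hypersensitivity and related serious adverse events on study drug, not a need for Ig after week 24.
- Section 8.2: points toward ordinary care but does not say that it overrides 6.5.

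Indicated Ig in washout is therefore a deviation under 10.1.8. Withdrawal under 7.2 is possible but discretionary.

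**Step 3. What happens to the data?** Section 7.1 continues to track infections and quality of life when study drug is halted. Section 7.2 commits to following patients who are off drug. Section 8.3.4 collects adverse events to the end-of-study visit. Collection is therefore largely secure. The open question is the analysis set. Section 9.3 names only a per-protocol set, and neither 9.3 nor 10.1.8 says which deviations exclude a patient.

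**Step 4. What does the ban protect?** The Schedule of Activities (1.3) has vaccination at week 36 and laboratory draws at weeks 36 and 40. Passive antibody from outside Ig would spoil those draws. No other data item needs the ban.

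**Step 5. Size.** The target of 10 treated patients (9.2) has no formula behind it, so there is no plan figure to reproduce. From the Schedule, per treated patient:
- SF-36 forms: V2 to V10 = 9 and V11 to V14 = 4, total 13. For 10 patients, 10 × 13 = 130.
- IgG draws: 2 at screening, 3 on therapy (weeks 4, 12, 24) and 2 off Ig (weeks 36, 40), total 7. For 10 patients, 10 × 7 = 70, of which 10 × 2 = 20 are off Ig.

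Let m be the number of treated patients who receive Ig after a serious washout infection. The protocol gives no rate, so m = 0 to 3 is an assumption. The table shows the worst case, in which the whole patient is excluded: forms = 130 − 13m and draws = 70 − 7m. The last two columns compare serious-infection proportions with Clopper-Pearson 95% intervals. They assume that the excluded patients are the only ones with a serious infection.

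| m | SF-36 forms left | IgG draws left | All treated | After exclusion |
|---|---|---|---|---|
| 0 | 130 | 70 | no change | no change |
| 1 | 117 | 63 | 1/10 = 10% (0.3 to 44.5%) | 0/9 = 0% (0 to 33.6%) |
| 2 | 104 | 56 | 2/10 = 20% (2.5 to 55.6%) | 0/8 = 0% (0 to 36.9%) |
| 3 | 91 | 49 | 3/10 = 30% (6.7 to 65.2%) | 0/7 = 0% (0 to 41.0%) |

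The infection count would fall by at least m, provided each of these infections needed antibiotics.

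With the fix, all 130 forms stay and the infection count is complete. At most 2m draws are flagged, so at least 68, 66 or 64 of 70 stand for m = 1, 2, 3. Off-Ig draws fall from 20 to no fewer than 18, 16 or 14.

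**Step 6. How likely is at least one case?** With assumed risk p per patient, the chance is 1 − (1 − p)^10. For p = 5%, 10% and 20% this gives 40%, 65% and 89%.

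**The case against.** The strongest reply is that the harm needs several steps that the protocol does not state. Outside Ig must be given, be classed as a deviation, lead to exclusion from the per-protocol set, and so remove the patient from each summary. Section 10.1.8 asks for deviations to be reported and corrected, not for patients to be removed. Withdrawal under 7.2 is optional, 4.4 defines completion rather than an analysis set, and a SAP could define per protocol narrowly. With 10 patients, descriptive statistics only and individual data that may be presented (9.4.5), one patient's infection could simply be shown. Keeping outside Ig out of washout is also sound for the week 36 and 40 results.

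Most of this stands, and it limits the point. A reader might infer that the affected patient must be excluded, that the data would be lost, or that the doctor has no way to treat. The protocol supports none of these: exclusion is possible but not stated, 7.1, 7.2 and 8.3.4 keep collection going, and 8.2 leaves room for ordinary care. A reader might also take the losses in the table as expected. They are worst cases on an assumed m.

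What the reply does not remove is the text itself. Section 6.5 is absolute and rests on a criterion that does not carry it. Section 9.3 names a per-protocol set and no other, even for safety. Protecting two draws does not require putting the rest of the patient's record at risk.

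**Conclusion.** The point holds as a conflict between stated rules with a possible outcome-dependent exclusion, and it should be fixed. Section 6.5 turns indicated Ig in washout into a deviation, in tension with 8.2. Section 9.3 then leaves room to drop the patient from the infection, adverse event and SF-36 summaries because of the event being counted.

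Each affected patient is 10% of the treated group. How many there would be is unknown, and if there are none nothing changes. Confidence is medium, because the result depends on how per protocol is defined and no SAP was available.

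It would go too far to say that the primary objective is threatened. That result is decided at screening and does not depend on a washout event. The on-treatment draws at weeks 4, 12 and 24 also predate the event, so their values are sound, although excluding the whole patient would still remove them from the summaries.

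**What to change.** 1. **Section 6.5.** Limit the reference to the exclusion criteria to study entry. Ask that outside Ig be avoided through week 40. Permit clinically indicated Ig started by the treating doctor in washout, recorded with start date and reason, and state that it is not in itself a deviation or a reason for withdrawal.
2. **Section 9.3.** Summarise safety, infections, SF-36 and on-treatment IgG and titres on all treated patients. For the off-Ig summary, flag or omit only IgG, titre and vaccine-response values obtained after outside Ig starts.

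The cost is a short text amendment, with no added visit, draw or patient. The downside is that up to 2 off-Ig draws (weeks 36 and 40) per affected patient cannot be interpreted. Outside Ig would spoil those draws in any case, and withdrawal before week 36 would lose them too.

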**6.5.1 Rescue Medication**

The study site will not be providing any rescue medications for the purposes of this study.

**7. Study intervention discontinuation and participant discontinuation/withdrawal**

**7.1 Discontinuation of Study Intervention**

Study intervention will also halt if patients experience a hypersensitivity reaction to the study drug. The study intervention will also be halted if there is any serious adverse event deemed related to the study drug by the study investigators. If the study intervention is halted, then pre and post vaccination titers will be obtained after subcutaneous immunoglobulin has been discontinued for 3 months. Infections will continue to be tracked through patient contact, the electronic medical record, and pharmacy data. Quality of life data will still be tracked through patient contact.

**7.2 Participant Discontinuation/Withdrawal from the Study**

The study intervention will be discontinued at any time a patient wishes to withdraw for any reason. Subjects will continue with medical care as prior to study enrollment.

All efforts will be made to continue to follow patients even if they are no longer receiving study drug. Study subjects may be withdrawn at any time based on the discretion of the investigator for safety, behavioral, or administrative reasons (including, but not limited to, an adverse event, lymphoma progression, protocol deviation, loss to follow up, non-adherence, or study termination).

In accordance with International Conference on Harmonisation (ICH) principles of Good Clinical Practice (GCP) the investigator always has the option to advise a subject to withdraw from the study over concerns of safety or subject well-being.

**7.3 Lost to Follow-Up**

A participant will be considered lost to follow-up if he or she fails to return for scheduled visits and is unable to be contacted by the study staff. If a participant fails to return to the clinic for a required study visit, the site will attempt to contact the participant and reschedule the missed visit, counsel the participant on the importance of maintaining the assigned visit schedule, and ascertain if the participant wishes to continue in the study.

Before a participant is deemed lost to follow-up, the investigator or designee will make every effort to regain contact with the participant, including 3 telephone calls and, if necessary, a certified letter to the participant’s last known mailing address. Should the participant continue to be unreachable, he or she will be considered to have withdrawn from the study with a primary reason of lost to follow-up

**8. Study Assessments and Procedures**

**8.1 Efficacy Assessments**

Efficacy will be assessed by the study drug increasing immunoglobulin levels, tetanus, diphtheria, and pneumococcal IgG levels, and study drug safety and tolerability in this population.

The secondary endpoint of quality of life will be assessed by the SF-36 quality of life assessment (please see attachment), which is a validated questionnaire. This will be administered monthly by the study coordinator.

The secondary endpoint of the frequency of humoral deficiency in patients with chronic lymphocytic leukemia will be assessed with the following laboratory data:

- IgG, IgM, IgA, IgE, CD4, CD8, CD3, and CD19 lymphocyte subsets
- Pre and post vaccine IgG responses 4 weeks apart to the following antigens: *Streptococcus pneumoniae*, diphtheria, tetanus, with a normal response defined as followed:
  - Strep pneumoniae (based on response to PPV):
    - If < 1.3, need to increase 2 fold to above 1.3 OR increase 4 fold
    - If > 1.3, need to increase 2 fold
    - Responses need to be demonstrated by 70% of serotypes
  - Diphtheria, normal response
    - 2 fold increase into protective range
  - Tetanus, normal response
    - 2 fold increase into protective range

Impaired vaccine response defined at abnormal response to any of the above antigens.

All blood specimens will be handled processed at the Rochester Regional Health laboratories as per usual clinical care. Laboratory data will be provided and explained to study subjects upon request.

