**Objectives:**

*Primary objective:*

To identify patients with CLL with humoral immunodeficiency despite serum IgG ≥ 400 mg/dL

*Secondary objectives:*

1. Efficacy of subcutaneous Ig replacement therapy in increasing Ig levels

2. Efficacy of subcutaneous Ig replacement therapy in increasing protective antibody titers for diphtheria, tetanus, streptococcus pneumoniae

3. Safety and tolerability of subcutaneous Ig replacement therapy

4. Quality of life (SF 36) on subcutaneous Ig replacement therapy

5. Track the number of infections requiring antibiotics, further characterized per severity as defined in previous studies.

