**1.3 Schedule of Activities**

Please see below.

|  | Screening | | Therapy with Ig Replacement | | | | | | | | | Wash Out Period | | | |
| --- | --- | --- | --- | --- | --- | --- | --- | --- | --- | --- | --- | --- | --- | --- | --- |
| Study visit | V1 |  | V2 | V3 | V4 | V5 | V6 | V7 | V8 | V9 | V10 | V11 | V12 | V13 | V14 |
| Week of study |  |  | 1 | 2 | 3 | 4 | 8 | 12 | 16 | 20 | 24 | 28 | 32 | 36 | 40 |
| Consent | X |  |  |  |  |  |  |  |  |  |  |  |  |  |  |
| Urine pregnancy test* | X |  |  |  |  |  |  |  |  |  |  |  |  |  |  |
| Medical history |  |  | X | X | X | X | X | X | X | X | X | X | X | X | X |
| Vitals |  |  | X | X | X | X | X | X | X | X | X | X | X | X | X |
| Physical exam |  |  | X | X | X | X | X | X | X | X | X | X | X | X | X |
| QoL (SF 36 form) |  |  | X | X | X | X | X | X | X | X | X | X | X | X | X |
| Pt teaching for Ig |  |  | X | X | X |  |  |  |  |  |  |  |  |  |  |
| Dispense study Ig |  |  |  |  |  | X | X | X | X | X | X |  |  |  |  |
| Pneumovax (PPV23) | X |  |  |  |  |  |  |  |  |  |  |  |  | X |  |
| Tetanus/diphtheria | X |  |  |  |  |  |  |  |  |  |  |  |  | X |  |
| IgG | X | X |  |  |  | X |  | X |  |  | X |  |  | X | X |
| IgM | X | X |  |  |  | X |  | X |  |  | X |  |  | X | X |
| IgA | X | X |  |  |  | X |  | X |  |  | X |  |  | X | X |
| IgE | X | X |  |  |  | X |  | X |  |  | X |  |  | X | X |
| IgG for 23 serotypes of strep pneumo | X | X |  |  |  | X |  | X |  |  | X |  |  | X | X |
| IgG for diphtheria | X | X |  |  |  | X |  | X |  |  | X |  |  | X | X |
| IgG for tetanus | X | X |  |  |  | X |  | X |  |  | X |  |  | X | X |
| T and B cell panel | X |  |  |  |  |  |  |  |  |  |  |  |  | X |  |

* Will be completed in women of child bearing age

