**3. Objectives and Endpoints**

1. The objective of this study is to identify patients with CLL who have serum IgG ≥400 mg/dL yet still have demonstrable humoral immunodeficiency.

To assess this objective, patients will undergo the following immune evaluation:

- Check serum IgG, IgM, IgA, IgE
- Check lymphocyte subsets, including CD4, CD8, CD3, and CD19
- Evaluate pre and post vaccine IgG responses 4 weeks apart to the following antigens: streptococcus pneumoniae, diphtheria, tetanus

Normal response to vaccination defined as follows:

- Strep pneumoniae (based on response to PPV)
  - If < 1.3, need to increase 2 fold to above 1.3 OR increase 4 fold
  - If > 1.3, need to increase 2 fold
  - Responses need to be demonstrated by 70% of serotypes
- Diphtheria, normal response
  - 2 fold increase into protective range
- Tetanus, normal response
  - 2 fold increase into protective range

Impaired vaccine response defined at abnormal response to any of the above antigens

2. Additional objectives of the study include to show that subcutaneous Ig replacement therapy is efficacious in increasing Ig levels and protective antibody titers in patients with CLL.

To assess this objective, IgG, IgM, IgA, IgE and IgG titers for streptococcus pneumoniae, diphtheria, tetanus will be checked periodically on therapy with subcutaneous Ig.

3. Another secondary objective will be to measure patient quality of life while on subcutaneous Ig replacement therapy.

To assess this objective, patients will complete SF-36 forms, which are a validated measure of patient quality of life.

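### Tetanus, diphtheria and pneumococcal titres are used to judge the drug after everyone is vaccinated against them, and the protocol names no reference draw and does not set aside antigens already protective before the first infusion

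*Protocol*

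**What the plan says.** The synopsis lists among the secondary objectives "Efficacy of subcutaneous Ig replacement therapy in increasing protective antibody titers for diphtheria, tetanus, streptococcus pneumoniae". Section 8.1 turns this into an assessment: "Efficacy will be assessed by the study drug increasing immunoglobulin levels, tetanus, diphtheria, and pneumococcal IgG levels". Section 9.1 adds the hypothesis that therapy will give protective titres to the same three antigens. Sections 9.4.1 to 9.4.3 specify descriptive statistics only, and sections 4.1 and 6.3 describe a single-centre case series without randomisation.

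The schedule in section 1.3 has both vaccines at V1, in the rows beginning "Pneumovax (PPV23) | X" and "Tetanus/diphtheria | X"; both are repeated at V13 (week 36), after therapy has stopped. Titres are drawn twice before V2: the rows begin "IgG for 23 serotypes of strep pneumo | X | X" and "IgG for tetanus | X | X". Section 3 explains the pair: "Evaluate pre and post vaccine IgG responses 4 weeks apart to the following antigens: streptococcus pneumoniae, diphtheria, tetanus". On-therapy titres follow at weeks 4, 12 and 24.

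Entry to therapy depends on this rule, given in sections 3 and 8.1: "Impaired vaccine response defined at abnormal response to any of the above antigens". A normal tetanus or diphtheria response is a 2-fold rise that ends in the protective range. A normal pneumococcal response must be shown by 70% of serotypes.

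**The concern.** The vaccines and the drug act on the same measurements, and the vaccines come first. Because one failed antigen is enough to qualify, a treated patient can arrive at V2 with vaccine-induced rises, and protective titres, for the antigens that were not failed. Two separate problems follow.

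- **Rise.** The protocol does not say which screening draw the on-therapy value is compared with. V1 is the only numbered visit before therapy, so an analyst could readily take it as baseline. The vaccine response would then be included in the drug effect.
- **Protection.** The hypothesis in section 9.1 is about protective levels. A normal tetanus or diphtheria responder is protective before the first infusion by the protocol's own definition, and would count in its favour whichever draw is the reference.

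At stake is how the titre results of about 10 uncontrolled patients can be read.

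**Working it through.** The protocol gives no alpha, power, effect size or SD, so there is no design figure to reproduce. The check asks whether mixed responses are possible among treated patients, how large the false rise is, and what remains under each choice of baseline.

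**1. Can a treated patient be a normal responder to some antigens?** Three antigens, each normal or abnormal, give 2³ = 8 patterns. All but one (all three normal) lead to therapy, so 7 qualify. Of these 7, 6 contain at least one normal response.

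Even a failed antigen can carry vaccine rises. For pneumococcus, 0.70 × 23 = 16.1, so 17 serotypes must respond. A patient with 16 of 23 responding is still classed as impaired.

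**2. How common might this be?** The synopsis expects 10 treated from 20 to 30 screened, a share s of 10/30 = 33% to 10/20 = 50%. Assume, for illustration only, that the antigens are independent with equal normal-response probability p, and write q = 1 − p. Then p = (1 − s)^(1/3), and

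P(at least one normal | treated) = (1 − q³ − p³) / (1 − p³).

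- s = 1/3: p = 0.874, result 99%.
- s = 1/2: p = 0.794, result 98%.
- For assumed p of 0.1, 0.2, 0.3, 0.5 and 0.7: 27%, 48%, 65%, 86% and 96%.

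If responses to the three antigens were fully correlated, the share would fall towards 0%. The documents do not fix it.

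**3. How large is the false rise?** Take a tetanus or diphtheria titre with the minimum normal response (2-fold), a drug effect of exactly zero, and a fraction w of the post-vaccine level lost by the on-therapy draw. The fold change is 2 × (1 − w) from V1 and 1 − w from the post-vaccine draw. The values of w are assumptions.

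| w | Fold from V1 | Fold from post-vaccine draw |
|---|---|---|
| 0% | 2.0 | 1.0 |
| 10% | 1.8 | 0.9 |
| 30% | 1.4 | 0.7 |
| 50% | 1.0 | 0.5 |

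The false rise exists only with V1 as reference. The post-vaccine draw removes it and, with waning, leans against the drug.

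**4. What remains under either baseline?** The protective-level summary. A normal tetanus or diphtheria responder is in the protective range at the 4-week draw, before V2. A patient protective at V1 whose titre does not double is classed abnormal, yet may be protective throughout. In neither case does being protective on therapy show a drug effect, and changing the reference draw does not alter that.

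**The case against.** The best answer is that the protocol already schedules what is needed. A full set of Ig levels and titres is drawn after vaccination and before V2, and a statement about the study drug increasing levels most naturally means change from the last pre-drug value. The baseline visit for a change score is commonly left to the SAP, which is not shown. The study is also a descriptive, proof-of-concept series of 10, intended to lead to controlled work, and section 9.4.5 allows individual data to be shown.

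Much of this stands. The inflated rise is conditional on using V1, and nothing in the protocol requires V1. Three stronger readings that a reader might infer are not supported:

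- *That vaccine and drug effects cannot be separated, or that the trial cannot support its drug conclusion.* The post-vaccine, pre-drug draw separates the 4-week vaccine response from what follows. Titre effects are one secondary objective, and the first secondary objective, raising Ig levels, is largely unaffected.
- *That antigens will be pooled across patients.* No section plans this, and the antigens are listed separately throughout.
- *That treated responders will show a 100% rise on therapy.* The 2-fold minimum belongs to the 4-week draw, applies only from V1, and shrinks with waning.

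What the objection does not answer is the protective-level criterion. That problem comes from the protocol's own rules (vaccination at V1, entry on any one antigen, protective titres as the hypothesis), not from a missing baseline definition.

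**Conclusion.** The point holds for antigen-specific titres and should be corrected; it does not bear on total IgG or the primary objective. With V1 as reference, the false rise for a normal tetanus or diphtheria responder is at least 2-fold at the 4-week draw; for a minimum responder it is 1.8- to 1.0-fold under assumed waning of 10% to 50%. With the post-vaccine reference there is no false rise, unless the vaccine response is still climbing after 4 weeks. The protective-level problem remains under either reference. How many patients are affected depends on how far responses to the three antigens go together: from nearly none under full correlation to 98–99% under independence at the planned screening yield.

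**What to change.** In sections 8.1 and 9.4.3, state that:

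1. on-therapy titre change is measured from the 4-week post-vaccine, pre-V2 sample;
2. it is reported by antigen and by vaccine-responder status for that antigen;
3. the share reaching protective levels is reported among patient-antigen pairs not protective at that sample, alongside the figures for all pairs.

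The fall from week 24 to V13, if shown, should be labelled descriptive only, because it mixes drug washout with waning of the V1 vaccine response.

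The cost is wording; every sample is already scheduled. The statistical price is smaller apparent rises, fewer pairs in the protection summary, a reference near the vaccine response so that waning leans against the drug, and some regression to the mean in the subset chosen for being non-protective. Showing the all-pairs figures beside the subset lets the reader judge that last effect.
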